### Study Design

This is an open-labeled, randomized controlled clinical trial with three treatment arms (see Figure 1 and Table 3). Children 6-36 months of age admitted to the Dhaka Hospital of the icddr,b with PD or who developed PD during their treatment period and failed to respond with milk suji—a low-lactose formula made from milk powder and rice powder—have been screened and enrolled in this study. The participant enrollment period lasted 18 months.

### Randomization

The permuted block randomization technique was followed to select treatment arms for each child. The randomization procedure was planned and set up by a scientist from the icddr,b who was not involved in the data collection. The randomization list containing the subject IDs and the corresponding group allocation remained concealed. IDs were chronologically assigned to each new study participant. After randomization, opaque envelopes containing the names of the allocated diet groups were opened.

**Table 3 table3:** Proposed dietary composition for this randomized controlled trial.

Ingredients per liter	Three-quarter-strength rice suji	Full-strength rice suji	Full-strength rice suji containing green banana
Green banana, g	N/A^a^	N/A	200
Glucose, g	30	30	25
Rice powder, g	40	60	50
Egg white, g	100	100	80
Soya bean oil, g	25	32	26
Sodium chloride, g	0.1	0.1	0.1
Magnesium chloride, g	0.5	0.5	0.5
Potassium chloride, g	1.0	1.0	1.0
Calcium carbonate, g	2.0	2.0	2.0
Energy, kcal/100 mL	57	70	70
Protein, g/100 mL	1.9	2.1	2.0
Osmolarity, mOsmol/L	296	298	<298
Protein energy ratio, %	13	12	11
Fat energy ratio, %	40	41	35

^a^N/A: not applicable.

### Collection of Baseline Information

All children with PD, either at admission or developed at some point during their treatment period, within the defined age group were screened for study eligibility criteria by the study physician. Parents or attending caregivers of those eligible children, depending on the inclusion and the exclusion criteria, were invited to provide their consent for enrollment of their children in the study. Parents and caregivers signed a written informed consent form (see Multimedia Appendix 1) and were provided with information about the study and its interventions, possible benefits and risks, and voluntary nature of participation, including the right to withdraw children at any time after the initial consent without providing any reason; after this, children were enrolled by the study physician. One copy of the signed consent document was given to the caregiver of each participant and another copy was kept for the study documentation. A pretested case record form was used to collect relevant medical history information, including nature and duration of illness and medication for current illness. The form was also used to collect information on sociodemographic characteristics, such as age, sex, religion, gestational age, parental age, parental education, parents’ occupations, drinking water source and sanitation, fuel use and smoking history, monthly family income, number of siblings, and number of rooms in the home. Information was also collected about each child’s feeding practice, such as their history of breastfeeding, formula feedings, or other complementary feedings, as well as immunization status and each child’s past history of pneumonia and diarrhea.

Data on clinical characteristics of participants was also collected. Clinical examination measurements recorded by the study physician included pulse and respiratory rate, axillary temperature, anthropometric measurements (ie, height, weight, mid-upper-arm circumference, weight-for-age Z-score, weight-for-length Z-score, and weight-for-height Z-score), chest auscultation, oxygen saturation, presence or absence of chest-wall indrawing, cyanosis, and mental status (ie, normal, irritable, or lethargic). Weight was measured using an electronic weighing scale with a precision of 0.1 kg; height/length was measured using a locally made length board with a precision of 0.5 cm by a trained and experienced nurse from the Dhaka Hospital of the icddr,b. Fever was defined when the axillary temperature was 38°C or greater. Respiratory rate was counted for a full 60 seconds by exposing the trunk when the child was awake and calm; the presence of lower-chest-wall indrawing was noted at the same time. Frequency and consistency of stool were monitored by either the study physician or a health worker every 8 hours up to the resolution of the diarrhea.

At discharge, caregivers were asked to come back with the children for a minimum of two, weekly follow-up visits.

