		Screening (day -3 to -1)	Enrollment (day 0)	Assessment and allocation (day 0)	Study diets (days 2-7)	First follow-up (days 14±3)	Second follow-up (days 21±3)

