### Clinical Management

Children with PD were admitted to the long-stay unit of the Dhaka Hospital of the icddr,b. Initial routine investigations were completed to identify the etiology of diarrhea by performing stool routine microscopic examinations and rectal swabs; if stool routine examinations were suggestive of invasive diarrhea, an appropriate antibiotic was provided according to hospital protocol. During this period, milk suji, a low-lactose milk and rice flour-based diet containing ~67 kcal and 1.3 g protein per 100 mL, was given as a routine diet. If the PD resolved with milk suji, the child was discharged with health advice. On day 4 (ie, 3 days after milk suji was given), if diarrhea did not resolve, the child was enrolled in the study and randomization was performed. The child received one of the three diets: full-strength rice suji containing green banana, full-strength rice suji alone, or three-quarter-strength rice suji alone. Children on all three diets were followed for 7 days. If there was deterioration of diarrhea (ie, either increased frequency or watery consistency) for 3 days or if the condition remained static for up to 7 days, the child’s status was declared as *treatment failure*. Children whose treatment failed received dietary intervention as per the standard management of diarrhea at the Dhaka Hospital of the icddr,b (see Figure 1).

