### Outcome Measures

#### Primary Outcome Variable

The primary outcome variable is the percentage of children who recovered from diarrhea by day 5 after being on the study diets.

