#### Secondary Outcome Variables

There were eight secondary outcome variables, as follows: (1) the percentage of children who recovered from diarrhea by day 7, (2) the consistency of stool on different days, (3) the frequency of stool on different days, (4) the outcome after being on the study diets for 1 week (eg, recovery time), (5) the number of hospital-acquired infections, (6) the rate of relapse within 14 days of follow-up, (7) the detection of enteric pathogens via the TaqMan assay and gut microbiota via 16S rRNA sequencing, and (8) the detection of proteomes and metabolomes related to PD.

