### Sample Size

Rabbani et al [20] conducted a study where they enrolled 5-12-month-old children; they found that their recovery rates from PD by day 4 on the green banana diet and rice suji was 78% and 23%, respectively. However, studies by Islam et al [13] and Mahfuz et al [37] found that a higher percentage of children recovered from PD after being given rice suji. There has been no study conducted where diets of rice suji with or without green banana were given to children 6-36 months of age. Considering these facts, we assumed that in 6-36-month-old children, the rate of recovery from diarrhea by day 5 in either of the intervention diet groups (ie, full-strength rice suji with or without green banana) would be 90% and that the rate of recovery in the control diet group (ie, three-quarter-strength rice suji) would be 65%.

With 80% power and a 5% type I error, and considering three treatment arms, we needed 40 children in each arm. If we enrolled 45 children in each arm, that would accommodate up to an 11% rate of attrition. Therefore, the total target sample size was 135 children (ie, 45 children × 3 arms).

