### Statistical Analysis

Data has been entered into a personal computer and will be analyzed using SPSS Statistics for Windows, version 20.0 (IBM Corp). Statistical analyses will include descriptive as well as analytical methods. We will compare different characteristics (eg, age, gender, diarrhea and its duration, stool consistency, presence or absence of blood, fast breathing, lower-chest-wall indrawing, and fever). We will also evaluate the PD outcome as *improved*, *death in hospital*, *relapse*, or *death during follow-up*. Categorical variables will be compared using the chi-square test. When the variables of interest are continuous and parametric, the statistical significance of group mean comparisons will be evaluated by analysis of variance (ANOVA). When the main outcome measures are continuous nonparametric variables, the statistical significance of differences will be determined using the Kruskal-Wallis test. The post hoc test will be done accordingly. A probability of less than .05 will be considered statistically significant. Strength of association will be determined by calculating relative risk and 95% CI. Our primary analysis is an intention-to-treat analysis comparing the groups. Survival analysis will also be carried out. Finally, regression analyses will be performed to reach more definitive conclusions.

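### Stool recording is said to stop at resolution, yet stool frequency and consistency are outcomes by day; analysed as observed, later days would compare only children still ill

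*Protocol article*

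**What the plan says.** The only rule for recording stools is in Collection of Baseline Information: "Frequency and consistency of stool were monitored by either the study physician or a health worker every 8 hours up to the resolution". Recording thus ends when the child recovers.

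Four other places bear on it:

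- **Secondary Outcome Variables** lists, as items 2 and 3 of eight, "2) the consistency of stool on different days, (3) the frequency of stool on different days".
- **Table 1** (under Ethics and Research Approval) marks both outcomes in the column headed "Study diets (days 2-7"), with one mark for the whole period.
- **Clinical Management** says: "Children on all three diets were followed for 7 days".
- **Statistical Analysis** assigns tests by type of variable: chi-square for categorical data, Kruskal-Wallis for continuous nonparametric data, and for continuous parametric data "the statistical significance of group mean comparisons will be evaluated by analysis of variance (ANOVA"). Intention to treat is stated for the primary analysis. The section does not say how days after resolution are treated.

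**The concern.** A stool outcome by day through day 7 needs a value for each child on each day. The recording rule supplies values only until the child recovers. From then on, whether a child has data depends on the trial's own main outcome, and recovery is assumed to be more frequent in two arms than in the third.

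A chi-square, ANOVA or Kruskal-Wallis test run on the records as they stand would, on later days, compare the unrecovered children of one arm with the unrecovered children of another. Randomization does not protect that comparison. It also leaves out the main way a diet would lower stool frequency on a given day, which is by turning ill children into recovered ones. Two named efficacy outcomes could then show little or nothing even though the diets differ.

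**Working it through.** **Inputs from the document.** The primary outcome is "the percentage of children who recovered from diarrhea by day 5 after being on the study diets". Sample Size assumes "full-strength rice suji with or without green banana) would be 90"% for the day-5 recovery rate in either intervention arm and 65% in the control arm, with 80% power, 5% type I error, 40 children needed and 45 enrolled per arm. (The Abstract gives a total of 145; the 45 per arm used here is the Sample Size figure.)

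**The plan's own figure.** The two-proportion formula with unpooled variance and two-sided 5% alpha gives

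n = (1.960 + 0.842)² × (0.90 × 0.10 + 0.65 × 0.35) / 0.25² = 39.87, so 40 per arm.

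Allowing for 11% attrition, 40 / 0.89 = 44.9, so 45. The stated sizes reproduce, and they do not depend on the point made here.

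**Who would have observed stool data on day 5.** Expected number still ill = n × (1 − recovery rate):

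| Arm | Still ill | Of 45 | Of 40 |
|---|---|---|---|
| Full-strength with green banana | 10% | 4.5 | 4 |
| Full-strength | 10% | 4.5 | 4 |
| Three-quarter-strength | 35% | 15.75 | 14 |
| Total | | 24.75 of 135 | 22 of 120 |

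About 18% of randomized children (24.75 / 135) would supply day-5 values, and the share is three and a half times as high in the control arm as in either other arm.

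**What that does to a daily comparison.** Let m_ill and m_rec be the mean daily stool counts of ill and recovered children. If m_ill is the same in every arm, then:

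- with all children included, the banana minus control difference is (0.10 − 0.35) × (m_ill − m_rec);
- with ill children only, the difference is m_ill − m_ill = 0.

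The document gives no stool counts, so the following are assumptions. Recovered children pass 0, 1 or 2 stools with equal chance (mean 1). Ill children pass 3 plus a Poisson count with mean 2, 3 or 4 (mean 5, 6 or 7), the same in all arms. The all-children difference is then −0.25 × 4 = −1.0, −0.25 × 5 = −1.25 or −0.25 × 6 = −1.5 stools per day.

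A simulation at 45 per arm (4,000 runs per setting, three-arm Kruskal-Wallis at .05) agrees:

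| Mean in ill children | Difference, all children | Power, all children | Difference, ill only | Rejection rate, ill only |
|---|---|---|---|---|
| 5 | −1.01 | 58.7% | −0.01 | 4.1% |
| 6 | −1.25 | 57.7% | 0.00 | 3.8% |
| 7 | −1.51 | 58.5% | 0.00 | 4.3% |

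Under these assumptions the observed-case test behaves as it would with no diet effect at all. The zero follows from assuming that ill children look alike in every arm. If those left unrecovered differ in severity between arms, the observed-case difference moves away from zero, and the document gives nothing from which to tell which way.

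**The case against.** The strongest reply is that the article never says recovered children are left out. It names two outcomes and a general list of tests. How days after resolution are scored is a derivation rule that often sits in a statistical analysis plan, which is not shown, and this is a condensed article. The 8-hourly rule may describe only the intensive monitoring, and the 7-day follow-up in Clinical Management may mean that observation went on. A child who no longer meets the Introduction's definition of diarrhea (three or more loose or watery stools in 24 hours) can also be scored as resolved without further counts.

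Much of this stands. An observed-case analysis is one possible analysis, not a stated one, and the bias is conditional on it. But the point does not rest on missing detail. A stated recording rule does not fit stated outcomes and a stated schedule, and an analysis plan can supply a scoring rule but cannot supply stools that were never recorded.

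A reader might go further in four ways that the document does not support:

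- **That the comparison would favour the wrong diet.** Nothing in the document shows a reversal, and the illustration gives a difference near zero.
- **That the plan breaks its intention-to-treat commitment.** That commitment is made for the primary analysis only.
- **That the primary outcome is undermined.** Recovery by day 5, recovery by day 7 and recovery time can all be read as first resolution, which needs data only up to that moment. What remains is narrower: a return of diarrhea in hospital soon after resolution may go unrecorded.
- **That a long run of separate daily tests is planned.** The document fixes no number of daily tests, so no false-positive rate can be computed from it.

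**Conclusion.** The recording rule and the by-day stool outcomes do not fit together as written and need to be reconciled. If the listed tests are applied to the observed records, later-day comparisons of frequency and consistency rest on a still-ill subset: about 25 of 135 children on day 5, split roughly 4.5, 4.5 and 15.75. The result is a selection-biased comparison of uncertain direction that omits the part of the diet effect acting through recovery.

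The counts rest on the protocol's planning rates and on recording having stopped at resolution as stated. The complete loss of the difference rests also on the assumed stool counts and on ill children being alike across arms. The direct effect is confined to two of eight secondary outcomes; the sample size is untouched. This is a moderate point that wording can settle, not a flaw in the trial's main comparison.

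**What to change.** Reconcile Collection of Baseline Information with Table 1, Clinical Management and Secondary Outcome Variables, by one of two routes:

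1. **If stool records continued through day 7**, say so and use them for every randomized child.
2. **If they stopped at resolution**, state before the analysis that every randomized child stays in each day's comparison. Recovered children are scored as resolved (best consistency category, lowest frequency rank), and the comparison is rank-based or ordinal, since a mean of counts is no longer defined. Kruskal-Wallis, already in the plan, would serve for frequency.

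A single longitudinal test per outcome in place of day-by-day tests is an option, not a requirement. Any ward records between resolution and discharge could be used to check for an early return of diarrhea.

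**Cost:** a few sentences and one derived variable. The Results section says data collection is complete, and the second route needs no new data. The main loss is that exact counts after resolution become a category or rank. Two limits should be acknowledged. An unrecorded early return would be scored as resolved. Also, on day 5 most children would share the top score (45 × 0.90 = 40.5 in each intervention arm, 45 × 0.65 = 29.25 in control), so these outcomes would largely repeat the recovery comparison.

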### Laboratory Tests

All laboratory tests were carried out according to the management outline of PD based on the previous studies [31-34], which include the following tests:

Stool for routine microscopic examination and culture for Vibrio, Salmonella, Shigella, and Campylobacter jejuni from rectal swab culture.Total and differential blood count.Chest x-ray of anteroposterior view for management of pneumonia.Serum electrolyte and creatinine if there is any clinical evidence of electrolyte imbalance or renal insufficiency.Blood culture for suspected septicemia, typhoid fever, prolonged febrile illness, or hospital-acquired infection.A rapid diagnostic test of stool by enzyme-linked immunosorbent assay (ELISA) for the diagnosis of Cryptosporidium spp and Giardia in selected cases, where the response is delayed or there is strong clinical suspicion.

With the aim to evaluate gut microbiota and proteomics in PD, additional investigations are planned as follows:

For gut microbiota analysis, fecal samples (2 g each) were collected from every child over the course of the study as follows: (1) on enrollment day, (2) at any time a diet was changed, and (3) at the time of discharge. Different types of microbiota of diverse groups (eg, Bacteroides, Prevotella, and Ruminococcus) will be tested by 16S rRNA sequencing.For the TaqMan assay to detect other enteropathogens causing PD, a fecal sample (2 g) on screening day was collected.

For proteomic and metabolomic assays, two plasma samples (150 µL each) were collected from 50 children over the course of the study as follows: (1) on enrollment day and (2) at the time of discharge from the study; samples are to be analyzed and tested by a collaborative institute (to be decided).

### Clinical Management

Children with PD were admitted to the long-stay unit of the Dhaka Hospital of the icddr,b. Initial routine investigations were completed to identify the etiology of diarrhea by performing stool routine microscopic examinations and rectal swabs; if stool routine examinations were suggestive of invasive diarrhea, an appropriate antibiotic was provided according to hospital protocol. During this period, milk suji, a low-lactose milk and rice flour-based diet containing ~67 kcal and 1.3 g protein per 100 mL, was given as a routine diet. If the PD resolved with milk suji, the child was discharged with health advice. On day 4 (ie, 3 days after milk suji was given), if diarrhea did not resolve, the child was enrolled in the study and randomization was performed. The child received one of the three diets: full-strength rice suji containing green banana, full-strength rice suji alone, or three-quarter-strength rice suji alone. Children on all three diets were followed for 7 days. If there was deterioration of diarrhea (ie, either increased frequency or watery consistency) for 3 days or if the condition remained static for up to 7 days, the child’s status was declared as *treatment failure*. Children whose treatment failed received dietary intervention as per the standard management of diarrhea at the Dhaka Hospital of the icddr,b (see Figure 1).

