**Methods:**

This open-labeled, randomized controlled study aims to enroll a total of 145 children with PD who have not been improving on a diet of milk suji. Children will be randomized into three different diet-specific groups: full-strength rice suji containing green banana, full-strength rice suji alone, and three-quarter-strength rice suji. The primary outcome is the percentage of children who recovered from diarrhea by day 5.

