#### Inclusion Criteria

Children aged 6-36 months, having diarrhea for 14 days or more (up to 29 days), either at admission or developed at some point during their treatment period in the hospital.Children able to take oral feeds at the time of randomization.

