## Discussion

The purpose of this clinical research is to improve the existing standard dietary treatment to manage PD. PD incurs a great amount of morbidity and has accounted for about 36%-56% of diarrhea-related mortality in low- and middle-income countries [3-7]. Current algorithm-based management was developed several years ago; different countries adopted these guidelines with modifications depending on their local and cultural backgrounds. This study will focus on whether a low-calorie, low-osmolarity, or green banana diet works best for the early resolution of diarrhea. The data gathered from this study will hopefully be of great interest to scientists, who may seek to modify the management strategy of PD or to pursue new elements in PD where proteomics- and metabolomics-based studies might provide more answers.

In conclusion, this study is expected to provide useful insights into the efficacy of green banana in the management of PD in children aged 6-36 months. If this diet results in improved outcomes in this setting, then we can assume that it would also be beneficial in other similar health care facilities. We will demonstrate whether this simple yet practical solution for PD works or not.

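### The abstract describes children not improving on milk suji, but the entry rule randomizes any child still unresolved after 3 days, so the population the result applies to is not clearly defined

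*Protocol article*

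**What the plan says.** Four places in the protocol article bear on who enters after the milk suji run-in.

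- **Abstract, Methods:** the trial enrolls "children with PD who have not been improving on a diet of milk suji".
- **Study Design:** children who "failed to respond with milk suji" were screened and enrolled.
- **Clinical Management:** the rule is that "On day 4 (ie, 3 days after milk suji was given), if diarrhea did not resolve, the child was enrolled in the study and randomization" took place. A child whose diarrhea resolved on milk suji was discharged. No other exit from the run-in is given.
- **Inclusion Criteria:** the list consists of an age range, the ability to feed by mouth when randomized, and a duration criterion, which begins "having diarrhea for 14 days or more (up to 29 days), either at admission or developed at some point during their treatment period in the". Neither this list nor the exclusion list contains a criterion on response to milk suji.

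The Discussion then concludes that "this study is expected to provide useful insights into the efficacy of green banana in the management of PD in children aged 6-36 months", without mention of the run-in. The Sample Size section assumes day-5 recovery of 90% on either full-strength diet and 65% on the three-quarter-strength diet. It attaches these rates to children of that age range and does not say what their run-in status is.

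**The concern.** A child who has not improved and a child who has not resolved are different children. The first description covers only those whose diarrhea stayed the same or got worse; the second also takes in those who are getting better slowly. A reader of the abstract, of Clinical Management and of the Discussion would come away with three different populations: non-improvers, everyone unresolved after 3 days, and all persistent diarrhea in the age range.

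At stake is the use of the result. A clinician deciding whether to change diet after milk suji needs to know whether the recovery rates come from children in whom milk suji did nothing or from a mixture that includes slow responders. A secondary question is whether the assumed recovery rates were chosen for the same population that was randomized.

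**Working it through.** **Step 1. Compare the rules on one child.** The Introduction defines diarrhea as at least three loose or watery stools in 24 hours. Take a hypothetical child who falls from 10 to 4 loose stools a day over the 3 days of milk suji.

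| Place | Is this child in? |
|---|---|
| Abstract | No: the child is improving |
| Study Design | Unclear: depends on what counts as a response |
| Clinical Management | Yes: 4 stools is still diarrhea, so not resolved |
| Inclusion Criteria | Not addressed |

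The clear conflict is between the abstract and Clinical Management. The Study Design phrase can be read as shorthand for unresolved. Against that reading, Clinical Management defines failure on the study diets as deterioration for 3 days or a static condition for up to 7 days, so there non-resolution alone is not failure.

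**Step 2. Reproduce the planned sample size.** Inputs from Sample Size: 65% vs 90%, 80% power, 5% type I error (taken as two-sided), 40 per arm, 11% attrition. With unpooled variance:

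n = (1.960 + 0.842)² × (0.65 × 0.35 + 0.90 × 0.10) / 0.25² = 39.9, so 40 per arm.

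40 / (1 − 0.11) = 44.9, so 45 per arm, and 45 × 3 = 135. The section's figures reproduce as a single pairwise comparison.

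**Step 3. What mixing could do, under stated assumptions.** None of these three is in the article:

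- a share f of those randomized is already improving;
- improving children recover by day 5 at the same rate r on every diet (r = 0.95 in the table);
- 90% and 65% apply to non-improving children only.

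Then the recovery rates are 0.90(1 − f) + rf and 0.65(1 − f) + rf. Their difference is 0.25(1 − f), whatever r is. Power at 40 per arm is Φ(difference / √[(p₁(1 − p₁) + p₂(1 − p₂)) / 40] − 1.960).

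| f | Full-strength diet | Three-quarter-strength diet | Difference (points) | Power |
|---|---|---|---|---|
| 0 | 90.0% | 65.0% | 25.0 | 80% |
| 0.1 | 90.5% | 68.0% | 22.5 | 73% |
| 0.2 | 91.0% | 71.0% | 20.0 | 66% |
| 0.3 | 91.5% | 74.0% | 17.5 | 57% |
| 0.4 | 92.0% | 77.0% | 15.0 | 47% |

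A pooled-variance formula with r from 0.90 to 1.00 starts at 77% and gives 70-72%, 61-65% and 52-58% for f = 0.1, 0.2 and 0.3.

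**Step 4. The alternative.** If 90% and 65% were meant for all children unresolved at day 4, improving children are already counted in both rates. The difference stays at 25 points, 40 per arm stands, and the loss is zero at any f.

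**The case against.** The strongest reply is that only Clinical Management states an operating rule, that it is explicit, and that the abstract merely paraphrases it loosely. Anyone who reads the Methods can tell who was randomized. The run-in also appears in Study Design, the flowchart is not visible in the text available, and a condensed article need not repeat every criterion. Enrolling every unresolved child is a legitimate design. The Discussion sentence is an expectation, not an analysis claim, and the sentence after it ties extrapolation to this setting and similar facilities.

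Much of this stands. The omission from the inclusion list would carry little weight alone, and the entry rule itself is not at fault. What does not fall away is that the abstract describes a narrower group than the rule admits, the formal criteria do not settle it, and the closing claim is broader than either.

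A reader might infer that improving children did enter in numbers and did weaken the contrast between diets. The article does not support that. It gives no share of improving children, does not say that they recover equally on all diets, and does not tie 90% and 65% to non-improvers; the 65% may already allow for spontaneous recovery. Nor can one infer bias between arms: the rule is applied before randomization, so it acts on all three arms alike.

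**Conclusion.** The inconsistency holds and is mainly one of population. The article describes non-improvers in one place, randomizes all children unresolved after 3 days of milk suji in another, leaves the run-in out of the inclusion criteria, and generalizes to persistent diarrhea at 6-36 months. The comparison between arms remains valid.

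An effect on power is possible but not established. It ranges from none, if the assumed rates describe everyone unresolved at day 4, to a fall from 80% to between 73% and 47% for improver shares of 10% to 40%, if the rates describe non-improvers alone and improvers recover at 95% on any diet. The article does not allow a choice within that range. The point is worth correcting because the article reports recruitment complete and results pending, so the wording and the analysis can still be aligned before the result is interpreted.

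**What to change.** 1. Reconcile the abstract, Inclusion Criteria, Study Design and Clinical Management so that one stated run-in criterion defines the children actually randomized. Which clinical criterion applied is for the investigators to confirm.
2. State in Sample Size which population the 90% and 65% rates describe.
3. Limit the Discussion's conclusion to that second-line population, that is, children who entered after the milk suji run-in.
4. Adjust the day-5 recovery comparison for stool frequency and consistency at randomization. The Statistical Analysis section names a chi-square test for categorical outcomes and regression in general terms; Collection of Baseline Information says both stool measures were monitored every 8 hours. Fix the model before the outcome data are examined and report the unadjusted relative risk beside it. The adjustment accounts for severity at entry; it does not identify which children had been improving.

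A sensitivity analysis by change in stool frequency over the 3 run-in days is optional. It is possible only if those counts were recorded, and the article does not say when the 8-hourly monitoring began.

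The cost is a few sentences, one adjusted analysis and a narrower claim. No new data are needed, provided the stool measures at randomization are on the case record form.
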